### Measurements

Climate data will be collected from Malaysian Meteorological Department (MMD) to confirm the variation in meteorological parameters. Spatial food and built environment data will be collected using geographic information system (GIS) for urban poor adolescents residing in PA/PPR in Kuala Lumpur, Malaysia. Two self-administrated Malay language questionnaires, a parental questionnaire and a adolescent questionnaire, will be developed and pre-tested. All parents and adolescents will be given instructions and explanations of the questionnaire variables. Anthropometric, physical fitness level, and haemoglobin level assessment will be conducted after the consent form and questionnaire are filled up. To ensure the accuracy of the data collected, participants will be re-interviewed and double check of questionnaires. Table 1 shows the details of the variables assessed during baseline and follow-up in this study.

**Table 1 Tab1:** Summary of data collection and timeline

Study variables	Baseline assessment (Northeast Monsoon)	Follow-up assessment (Southwest Monsoon)
**Parental Questionnaire**		
Parental/Guardian’s information		
Age	*	
Ethnicity	*	
Marital status	*	
Educational attainment	*	
Occupation	*	*
Monthly household income	*	*
Adolescents’ information		
Age	*	
Date of birth	*	
Sex	*	
Ethnicity	*	
Educational Attainment	*	
Household size	*	
Number of school-going children	*	
Duration of living in PA/PPR	*	
Medical illness or disabilities	*	
Medication or supplement use	*	
18-item USDA Household Food Security Module	*	*
Perceived Nutrition Environment Measures Survey	*	*
Physical Activity Neighbourhood Environmental Survey	*	*
**Adolescent’s Questionnaire and Assessment**		
Pubertal Development Scale	*	*
2-day diet recall	*	*
Eating Behaviours Questionnaire	*	*
Physical Activity Questionnaire for Older Children	*	*
Screen time	*	*
Step counts	*	*
Changes in lifestyle-related behaviour during COVID 19 pandemic	*	
Modified Harvard step test	*	*
Body weight	*	*
Height	*	*
Waist circumference	*	*
Body fat percentage	*	*
Haemoglobin level test	*	*

#### Climate data

Climate data will be assessed through the monthly mean data for meteorological parameters, including rainfall (mm), temperature (°C), and relative humidity (%) from the Malaysian Meteorological Department from the monitoring stations located in Petaling Jaya, FRIM Kepong, KLIA Sepang, Subang, and Hulu Langat. Climate data during the actual data collection period will be assessed for both Southwest and Northeast monsoon seasons. Besides, climate data of selected meteorological parameters for the past 10 years will also be extracted to identify the climate trend for both monsoon seasons and to confirm any climate variation over the years.

#### Spatial food and built environment

Spatial food and built environment are defined using a buffer zone area of defined geographic distance from the low-cost flats. QGIS 3.4 Madeira will be used to generate walking-distance circular buffers for a distance of 1000 m on-street network away from residential flats. These are the common buffer sizes applied in active research transport as this is the distance that can be covered by a 10–15-minute walk [42]. The exact address of each selected flats is required, which will be converted into geographic coordinates. The spatial data of all food and built establishments within the residential neighbourhood environment are geocoded to obtain latitude and longitude, where on-site data collection will be performed using a Qmini A7 High-precision (country that produce it) GIS handheld device. Types of food establishments included are supermarkets (e.g., AEON, GIANT, TESCO, large local wet markets, etc.), fast-food restaurants (e.g., KFC, Pizza Hut, McDonald’s, Texas Chicken, etc.), restaurants, convenience stores (e.g., 7-eleven, KK mart, Shell Mart, etc.), street food and specialty food stores (e.g., bakeries, fruit and vegetables, gourmet, meat and fish markets). Built establishments for physical activity included parks and public recreational facilities (e.g., soccer fields, basketball courts, community centers, pools, and playgrounds). Besides, the location of bus stops and the station will also be collected. The assumption is made that no substantial changes in the distribution and number of this food and built establishments throughout the study.

Using the geocoded data, the following spatial neighbourhood food and built environment indicators will be created: (1) density of food and built establishments within 1000 m network buffer zones; and (2) proximity to food and built establishments (closest distance, via the street network, from PA/PPR to each type of food and built establishment). The density and proximity to the food and the built establishments will be determined in QGIS software using the Buffer, Mapping, and Count Point analysis tools.

#### Adolescent’s questionnaire and assessment

##### Physical development

Pubertal Development Scale (PDS) will be used to assess the pubertal status of adolescents [43, 44]. A total of five items are assessed in PDS to rate the growth spurt, body hair growth, and skin changes using a four-point scale: “not yet started” (1), “barely started” (2), “definitely started” (3), “seems complete” (4), and “I don’t know” (0). On a similar scale, boys will be asked to rate their development of facial hair and voice change, whereas girls rated their breast development and whether they have reached menarche, present (4) and absent (1). Based on the sum of the scores, adolescents will be categorized into pre-pubertal, early pubertal, mid-pubertal, late pubertal, and post-pubertal [43, 44].

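### Pubertal stage is set from a sum in which 'I don't know' scores 0, so, applied as written, an uncertain answer can only leave the stage unchanged or make it less mature

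*Protocol article*

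**What the plan says.** All the scoring text is in the protocol article under Physical development.

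- The instrument has five items. Three are common to both sexes: "A total of five items are assessed in PDS to rate the growth spurt, body hair growth, and skin changes".
- They are rated "using a four-point scale: “not yet started” (1), “barely started” (2"), continuing to 3 for 'definitely started' and ending with "seems complete” (4), and “I don’t know” (0").
- Two items depend on sex. For boys: "On a similar scale, boys will be asked to rate their development of facial hair and voice change". Girls rate breast development and report "whether they have reached menarche, present (4) and absent (1").
- The stage comes from the total: "Based on the sum of the scores, adolescents will be categorized into pre-pubertal, early pubertal, mid-pubertal, late pubertal, and post-pubertal". Two references are cited for the scale; the cut-offs are not printed.

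Table 1 schedules the "Pubertal Development Scale" at both the baseline and the follow-up visit. Neither Study aim nor Data management and analysis names pubertal stage as an outcome or a covariate.

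**The concern.** An answer of 'I don't know' carries no information about maturity. The printed codes place it one step below the least mature real answer, and the printed rule then adds the codes up. An adolescent who is unsure about an item is therefore scored as less developed than one who says that the change has not begun. The error does not average out, because it has one direction. It is also largest for the most mature, who lose the most points per uncertain answer.

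The sample is aged 10 to 17 and so spans puberty, and this scale is the only maturity measure repeated at both visits. What is at stake is the reported distribution of pubertal stage at each visit, and any later analysis that adjusts for stage or compares it between visits.

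**Working it through.** There is no stated figure to reproduce, so the check is arithmetic on the printed codes.

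**Inputs (all from Physical development).** Five items; substantive codes 1 to 4; don't-know code 0; menarche coded 4 or 1 only; stage taken from the unadjusted sum.

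**Valid range.** With every item answered, the minimum is 5 × 1 = 5 and the maximum is 5 × 4 = 20. This holds for girls too: four items at 1 to 4 plus menarche at 1 or 4 gives 5 to 20.

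**Shift per don't-know answer.** Replacing a true answer v by 0 changes the sum by 0 − v. With v from 1 to 4, the shift lies between −1 and −4 and is never positive.

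**Uniform profiles.** With every item truly at level L and k don't-know answers, the printed rule gives (5 − k) × L. Prorating gives the mean of the answered items × 5, which is L × 5 for any k below 5.

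| True level on all items | k = 0 | k = 1 | k = 2 | Prorated, k = 0, 1 or 2 |
|---|---|---|---|---|
| 4, seems complete | 20 | 16 | 12 | 20 |
| 3, definitely started | 15 | 12 | 9 | 15 |
| 2, barely started | 10 | 8 | 6 | 10 |
| 1, not yet started | 5 | 4 | 3 | 5 |

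Two results stand out. An adolescent at 'definitely started' with two uncertain answers scores 9, below one who is at 'barely started' on everything (10). The bottom row gives sums under 5, which no fully answered form can produce.

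**Lowest possible sums.** A boy answering 'I don't know' throughout scores 0. A girl can do so on at most four items, so her lowest sum is 0 + 1 = 1 before menarche and 0 + 4 = 4 after it. All three are below 5.

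**Direction of the stage error.** Whatever the cut-offs, if higher sums map to later stages, a lower sum maps to the same stage or an earlier one. The direction therefore does not depend on the missing cut-offs; the number of adolescents who change stage does.

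**Between visits.** Take an adolescent truly at 'definitely started' on all items at both visits. One don't-know answer at baseline and none at follow-up gives 12 then 15, an apparent gain of 3 points with no biological change. The reverse pattern gives an apparent loss of 3. Spurious progress across the cohort therefore needs don't-know answers to become less frequent at follow-up; the article gives no rate for either visit.

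**The case against.** The strongest reply is that the 0 was never meant to be added. The article calls the format a four-point scale, and 0 lies outside four points running from 1 to 4, so it may be only a data-entry code for non-response. The cited references may say how to handle it, and a condensed article need not repeat item-level missing-data rules. That reading is possible, but nothing in the text supports it. The 0 is printed in the same list as the other codes, and the next step is a plain sum of the scores. Where scoring exceptions apply elsewhere, the article prints them: the section on lifestyle change during COVID-19 lists reverse-scored items and the separate scoring of items 3 and 18. The objection is thus not about a detail left out; the two printed statements, taken together, give a wrong score.

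Other parts of the reply stand:

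- A reader might infer that someone answering 'I don't know' throughout is certain to be classed pre-pubertal. The article does not support that. No cut-offs are printed, a sum of 0 may fall outside every category, and a girl cannot score 0 as the codes are printed.
- A reader might also infer that the rule manufactures pubertal progress between the monsoon seasons. That is conditional on a fall in don't-know answers, for which the article gives no evidence. The re-interviewing and double-checking described under Measurements may reduce unresolved answers.
- Using pubertal stage to control for growth in the season comparison would be natural, but the article does not say that it will. Height-for-age and BMI-for-age Z-scores, which define nutritional status, do not use this scale.

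**Conclusion.** The point holds as a scoring error in the printed rule. Each 'I don't know' lowers the sum by 1 to 4 points, so that 20 becomes 16 or 12 with one or two such answers, and it moves the stage, if at all, towards pre-pubertal. Up to five items are exposed for boys and up to four for girls.

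This rests on two assumptions: that the sum is taken literally over the printed codes, and that the unprinted cut-offs are ordered. How many adolescents change category cannot be computed without the cut-offs and the don't-know rate.

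The consequence is confined to the reported stage at each visit and to any adjustment for, or comparison of, stage. Since Data management and analysis names no such use, the effect on the main seasonal results is probably small. The change is still worth making, because it is cheap and the printed rule has no evident advantage.

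**What to change.** State that 'I don't know' is a missing answer, not a score of 0, and apply the same rule at both visits. Then choose one of two options in advance:

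1. Prorate (mean of answered items × 5) when a pre-set minimum number is answered, for example when at most one item is missing, and set the stage to missing otherwise. A rounding rule is needed, because prorated sums need not be whole numbers.
2. Set the stage to missing whenever any item is unknown.

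The threshold of one missing item is a suggestion; the article gives no basis for a particular value. Prorating also assumes that the unknown item resembles the answered ones. Reporting the number of don't-know answers per visit would show whether the issue matters in practice.

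The cost is one line of scoring and a missing stage for some adolescents, probably few. No new data are needed: 0 is used for nothing else on this scale, so these answers can be identified if item-level codes were kept. The section on status and timeline says that the data had not been processed for analysis at submission. If 0 was always intended as a missing code, one sentence saying so, with the rule for the sum, settles the point.

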##### Physical activity and fitness level

Physical activity level will be assessed subjectively using the physical activity questionnaire for older children (PAQ-C) [45]. The Malay version of PAQ-C had been validated among adolescents aged 10–17 years old [46]. A total of 10 items are assessed in the PAQ-C to assess the general levels of physical activity of adolescents over the past seven days and will be scored based on a 5-point scale ranging from ‘no activity’ (1), and ‘7 times or more’ (5). The mean total physical activity score will be calculated and classified into low (1–2.33), moderate (2.34–3.66), and high (3.67–5) [47]. Additionally, screen time such as watching television, using a computer, and playing video games of an adolescent during weekends and schooling days will be assessed as well and further classified into screen time less than two hours and more than two hours [14].

In addition, a subsample of 50 adolescents will be randomized for objective measurement of physical activity level using a pedometer (YAMAX Digi-Walker SW-700) [48]. Adolescents are assigned a pedometer, elastic belt, and a 4-day pedometer diary. The pedometer will be distributed on the same day of data collection and adolescents are instructed to self-monitor their physical activity for four consecutive days with at least one weekend day [49] by wearing the pedometer at the waist from the time they wake up until they go to bed at night, excluding water-based activities and bathing time. Subjects are requested to record the day-end values for pedometer steps, other readings displayed, and non-ambulatory activities (e.g., swimming, cycling, etc.) and to reset to zero every day. A reminder will be sent to the subjects or their parents/guardians at least once throughout the data collection period.

The physical fitness test will be conducted using a modified Harvard Step Test [50]. This method was used in previous local studies [51, 52]. Subjects are requested to wear light clothes in order to carry out the test. Subjects are instructed to step up and down on a 30 cm high step box with both feet for a maximum of five minutes or until fatigue compelled him or her to stop and rest. Immediately, the heart rates at zero, one, and two minutes of rest will be measured using an automatic blood pressure monitor (OMRON HEM-7120 Automatic Blood Pressure Monitor, OMRON HEALTHCARE Co., Kyota, Japan) and recorded, as well as the total duration of exercise. Physical fitness scores will be calculated and classified into “unacceptable” (< 65), “marginally acceptable” (65–79), and “acceptable” (≥80) [50].

##### Dietary assessment

A two-day 24-hour dietary recall which comprised one weekday and one weekend, is used to determine the food consumption and nutrients intake of subjects. The dietary recall method is carried out through face-to-face interviews. Subjects will be asked to recall and report foods and beverages consumed. Detailed information including types, brand names of commercial products, food preparation method as well as the amount consumed with the aid of a set of standard household measurements such as spoons, teaspoons or tablespoons, cups, glasses, bowls, and plates, along with the use of the Food Atlas book [53]. Dietary intake data will be analyzed using the Nutritionist Pro™ Diet Analysis Software Version 4.0 (Axxya Systems, Stafford, TX, USA) based on the food listed in the Malaysian Composition Database Nutrient Composition of Malaysian Food. This was then further evaluated for the overall diet quality of the subjects using the Standardized Malaysian Healthy Eating Index (S-MHEI) [54].

The S-MHEI consisted of 11 components, including eight food groups (total grains, whole grains, fruits, vegetables, meat/poultry/eggs, legumes/nuts, and milk/milk products) and three nutrient groups (total fat, sodium, and sugar). The scoring of these components is calculated based on the serving size and nutrient intake recommended by the Malaysian Dietary Guidelines [55] and Malaysian Dietary Guidelines for Children and Adolescents [56]. The score of each component ranged from 0 to 10, which is calculated proportionately for the in-between whole-number responses. However, as total grains and whole grains are from the same food group, the maximum score provided to each component is five to avoid scoring overlap. The total S-MHEI score is obtained by summing up the score of each component with a score range of 0 to 100. A higher S-MHEI score indicates better diet quality. Based on the maximal dietary intake score of 100, the subjects will be categorized as ‘good diet quality’ (> 80%), ‘diet quality needs an improvement’ (51–80%) and ‘poor diet quality’ (< 51%) [54].

The frequency of meal consumption will be assessed using six items from the Eating Behaviours Questionnaire (EBQ) [57]. Adolescent is required to indicate the frequency of each meal consumption and snacking behaviour, including breakfast, morning snack, lunch, evening snack, dinner, and supper, based on an 8-point scale ranging from never (zero) to every day (7 times) in a week.

##### Changes in lifestyle-related behaviour during the COVID-19 pandemic

The 20 items short questionnaire developed by Kumari et al. [58] will be used to assess the changes in lifestyle-related behaviour of adolescents during the COVID-19 pandemic. Subjects will be asked in assessing the changes in dietary habits (intake, meal pattern, and snack consumption), physical activity (duration and type), and sleep pattern (duration and quality), using a 5-point Likert scale ranging from “significantly decreased” (+ 2) and “significantly increased” (− 2). It is noted that some of the items (Item 4–5, 11–16, 19) are reverse scored. Besides, items 3 and 18 are scored as “grossly similar” (0), “slightly increased/decreased” (− 1), and “significantly increased/decreased” (− 2). The total score will be calculated and a higher score indicating shifting toward a healthy lifestyle during the COVID-19 pandemic.

##### Anthropometric measurements

All equipments will be calibrated before the measurements are performed. The body height of subjects will be measured using a calibrated vertical stadiometer (Seca 213 portable stadiometer, SECA GmbH & Co., KG. Hamburg, Germany), whereas weight and body fat percentage will be measured using the Bioelectrical Impedance Analyzer (OMRON HBF-375 Karada Scan Body Composition Monitor, OMRON HEALTHCARE Co., Kyota, Japan). Both height and weight measurements are recorded to the nearest 0.1 cm and 0.1 kg, respectively. The nutritional status of adolescents will be determined based on Z-scores for height-for-age (HAZ) and BMI-for-age (BAZ) of WHO growth reference 2007 for adolescents between 5 and 19 years old using WHO AnthroPlus version 1.0.3 software (WHO, Geneva, Switzerland). The classification as followed, stunting (HAZ < -2SD), normal height (HAZ > -2SD), thinness (BAZ < -2SD), normal weight (−2SD ≤ BAZ ≤ +1SD), overweight (+1SD < BAZ ≤ +2SD), and obesity (BAZ > +2SD) [59]. The body fat percentage will be classified using percentile scores for sex and age based on the findings by McCarthy et al. [60] into underfat (<2nd percentile), normal (2nd – 85th percentile), overfat (>85th – 95th percentile), and obese (>95th percentile).

Waist circumference will be measured at the midway between the lowest rib and the superior border of the iliac crest as recommended by WHO [61] using a non-elastic SECA 201 Ergonomic circumference measuring tape (DECA GmbH & Co., Hamburg, Germany) to the nearest 0.1 cm. A cut-off point of the 90th percentile of waist circumference percentile classification for Malaysian children and adolescents [62] will be used to identify abdominal obesity. For adolescents aged 17 years and above, WHO/IASO/IOTF (2000) for Asian cut-off [63] will be used instead. Abdominal obesity was defined as ≥90 cm for men and ≥ 80 cm for women. Mean average values will be used for data analysis.

##### Anaemia status assessment

A haemoglobin level test will be performed to identify the anaemia status of each adolescent by using the HemoCue haemoglobinometer (HemoCue® Hb 201+ System, Angelholm, Sweden), point-of-care testing on capillary blood samples. Anaemia status and level of severity are determined according to the age and gender-specific haemoglobin cut-off point as defined by WHO [64]: (i) < 115 g/L for 5 to 11 years of age; (ii) < 120 g/L for 12 to 14 years of age and non-pregnant women (15 years of age and above); (iii) < 130 g/L for men (15 years of age and above).

#### Parental questionnaires

##### Sociodemographic background

Sociodemographic data will be collected for both adolescents and parents using a self-administrated questionnaire. Adolescent information includes age, sex, date of birth, ethnicity, household size, number of school-going children, duration of living in PA/PPR, medical illness or disabilities, medication, and supplement use, whereas parental/guardian information includes age, educational attainment, marital status, occupation, and monthly household income.

##### Household food security status

Food security status is measured using the United States Department of Agriculture (USDA) 18-item Household Food Security Survey Module (HFSS) which captures all severity levels of household food security and children’s condition in the household [65]. This section of the items will be filled by the parents or the guardians as parents or guardians will be responsible for purchasing or preparing the food for the household and the adolescent. A total of 18 items will be asked and answers of “yes”, “often true”, “sometimes true,” “almost every month,” and “some months but not every month” are coded as affirmative (1 point). The sum of affirmative responses to the 18 questions is referred to as the household’s raw score. With a maximum score of 18, subjects will be categorized into high food security (0), marginal food security (1–2), low food security (3–7), and very low food security (8–18). Subjects will be further dichotomized into two groups, the food secure group (high or marginal food security) and the food insecure group (low or very low food security) [65].

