Similarly, built environments, including the combinations of coexisting stimuli such as recreational facilities, green spaces, parks, land use, and transport infrastructures, influence an individual’s ability to achieve the recommended level of physical activity. Urbanization had to cause the reduction of physical activeness due to the urban environmental quality and the setting [33], whereby high-density traffic, limited sidewalks, parks, and recreational facilities as well as overcrowding and safety in the neighbourhood such as crime and violence are commonly reported as the significant barriers that could discourage, or crease active living and causing changes in lifestyle behaviour [34, 35]. Other important environmental variables include mixed land use, transportation system, and the density of built spaces which are related to the walkability of a neighbourhood, consequently, weight status [36].

As Malaysia is located close to the equatorial line, hence no extreme weather changes can be observed and are free from inter-seasonal variability as seen in four-season countries [10]. However, the climate system of Malaysia is largely influenced by the Southeast Asia Maritime Continent monsoon, which consists of two monsoon regimes, Southwest Monsoon (summer monsoon, late May to September) and Northeast Monsoon (winter monsoon, November to March) [37, 38]. With this, it is hypothesized that seasonal variation in food security, dietary consumption, and physical activity behaviours that leads to nutritional changes, as observed in the four-season countries, may also be observed in Malaysia during the two monsoon seasons. Nevertheless, these anticipated changes and their long-term effects were rarely studied in Malaysia. Additionally, most of the research on seasonality are generally focuses on young children [24, 25, 39, 40] and adults [22, 23], and adolescents are often understudied despite their apparent vulnerability is observed. With this, It is unclear of the possible long-term impact of climate variability on the changes in nutrition-related components in Malaysia. This makes the need to study the effects of seasonal variability on malnutrition and its associated factors especially among the urban poor adolescent population in Malaysia.

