## Methods

### Study aim

The main aim of the study is to examine the seasonal variation in food security, lifestyle factors, neighbourhood environmental factors, and nutritional status of the urban poor adolescents in Kuala Lumpur, Malaysia. To achieve the aim, the specific research objectives to be investigated in the study are as follows:To determine the food security, lifestyle factors, neighbourhood environmental factors, and nutritional status of the urban poor adolescents in Kuala Lumpur, Malaysia.To determine the seasonal differences in food security, lifestyle factors, and nutritional status among urban poor adolescents in Kuala Lumpur, Malaysia.To determine the effects of season on food security, lifestyle factors, neighbourhood environment, and its effects on the nutritional status of the urban poor adolescents in Kuala Lumpur, Malaysia.

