### The status and timeline of the study

The first adolescent was enrolled on the 1st of November 2021. The recruitment process and baseline data collection were completed on the 30th of April 2022. At the time of submission, all de-identified subjects data are kept and manage but have not yet been processed for analysis.

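### Food security is scored with month-frequency answers and no stated recall window, so a difference between the two visits may not be attributable to the monsoon

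*Protocol article*

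**What the plan says.** Under Household food security status, the Protocol article names the instrument: "Food security status is measured using the United States Department of Agriculture (USDA) 18-item Household Food Security Survey Module (HFSS". Five answers score one point. Three carry no time unit (a plain yes, and the two degrees of a statement being true). The other two are frequencies in months, one for nearly all months and one for only some of them; the list ends "some months but not every month” are coded as affirmative (1 point". The score follows: "The sum of affirmative responses to the 18 questions is referred to as the household’s raw score". It is then cut into four categories and into secure versus insecure. The section gives no reference period and mentions no adaptation to a season.

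Table 1 lists "18-item USDA Household Food Security Module" at both baseline and follow-up. Under Study aim, Objective 2 reads "To determine the seasonal differences in food security, lifestyle factors, and nutritional status among urban poor adolescents", and Objective 3 asks for the effects of season on food security among other factors. Data management and analysis assigns a paired-samples t-test to the difference between the monsoons and a generalized linear mixed model to the seasonal effects.

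The Background dates the seasons: "Southwest Monsoon (summer monsoon, late May to September) and Northeast Monsoon (winter monsoon, November to March". On timing, the status section says "The first adolescent was enrolled on the 1st of November 2021" and that baseline data collection ended on 30 April 2022. Follow-up falls in the Southwest Monsoon, without dates.

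**The concern.** A respondent can tell the two month-frequency answers apart only if the question covers several months. In a one-month window neither answer has meaning. The visits are on average about six months apart if follow-up took place in the next Southwest Monsoon. A look-back of that order, filled in during one monsoon, reaches into the other. The label attached to the form (Northeast or Southwest) would then describe when it was completed, not the period it reports on.

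Other measures do not have this problem: physical activity is recalled over seven days and diet by 24-hour recalls.

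Food security comes first in the title and the aim. The Background names it, with diet and physical activity, among the behaviours expected to vary by season and lead to nutritional change. If the look-back mixes the seasons, a real seasonal swing is diluted or lost. A significant paired difference could then be reported as a monsoon effect when it reflects something else. The Discussion itself concedes that pandemic effects on food security may have been overlooked.

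**Working it through.** The plan states no figure on this point to reproduce, so the check is a calendar count.

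**Inputs from the Protocol article**
- Northeast Monsoon: November to March.
- Southwest Monsoon: late May to September.
- Baseline: 1 November 2021 to 30 April 2022 (181 days).

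**Assumptions**
- The Southwest Monsoon starts on 25 May.
- Follow-up takes place in the next Southwest Monsoon, 25 May to 30 September 2022 (129 days).
- Visit days are spread evenly over each period.
- The look-back is 1, 3, 6, 9 or 12 months (30, 91, 183, 274 or 365 days), because the documents do not give it.

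**Formula.** For a visit on day *d* and a window of *w* days, Northeast share = (Northeast days among the *w* days before *d*) / *w*, and likewise for Southwest. Average over visit days. The Northeast contrast is baseline minus follow-up; the Southwest contrast is follow-up minus baseline. A contrast of 1 means clean separation; 0 means both visits cover the same amount of that season. Differences are taken before rounding.

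| Window (months) | NE share, baseline | NE share, follow-up | NE contrast | SW share, baseline | SW share, follow-up | SW contrast | Visit days touching both monsoons, baseline / follow-up |
|---|---|---|---|---|---|---|---|
| 1 | 0.83 | 0.00 | 0.83 | 0.00 | 0.88 | 0.88 | 0 / 0 |
| 3 | 0.72 | 0.06 | 0.66 | 0.11 | 0.64 | 0.53 | 0.33 / 0.28 |
| 6 | 0.48 | 0.36 | 0.12 | 0.34 | 0.35 | 0.01 | 0.83 / 0.99 |
| 9 | 0.36 | 0.50 | -0.14 | 0.43 | 0.25 | -0.17 | 1.00 / 1.00 |
| 12 | 0.41 | 0.41 | 0.00 | 0.35 | 0.35 | 0.00 | 1.00 / 1.00 |

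Counting six months as 182 days instead of 183 gives 0.13/0.01.

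**Twelve months.** Any 365-day window holds 151 Northeast days (151/365 = 0.41) and 129 Southwest days (129/365 = 0.35), whatever the visit date. The contrast is therefore zero for every pair of visits.

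**Overlap at twelve months.** The possible gap between visits is 25 to 333 days, mean 179. Shared fraction = (365 - gap)/365:
- (365 - 25)/365 = 0.93
- (365 - 333)/365 = 0.09
- (365 - 179)/365 = 0.51 on average

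The windows are not identical, so scores can change. The unshared parts are the same calendar dates one year apart. A change in them is therefore a year-on-year change rather than a seasonal one.

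**Three months, near season onset.** A form completed on 1 November 2021 looks back over August to October: 61 of 92 days are Southwest and none Northeast. A form completed on 25 May 2022 looks back over 25 February to 24 May: 4 + 31 = 35 Northeast days and no Southwest days. Each would carry the wrong season's label.

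**The case against.** A reader might infer more: that the module has a twelve-month recall, that both visits necessarily look back over both monsoons, and that the seasonal contrast is zero by construction, so a null result would mean nothing. The documents do not support that.

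- **The window is not stated.** Twelve months could come only from outside knowledge of the instrument. At three months most of the contrast survives, and only about a third of baseline and just over a quarter of follow-up visit days touch both monsoons. Every visit does so only at nine and twelve months.
- **The day count is not a result about scores.** Equal season coverage implies zero expected contrast only if respondents weight all months equally. If recent months weigh more, some seasonal signal could remain.
- **Not every answer refers to months.** Two of the five affirmative answers do, and the article does not say how many of the 18 items use them.
- **The questionnaire is not shown.** Malay versions were to be developed and pre-tested, and an article may leave recall wording to them.
- **Part of the plan is unaffected.** Objective 1 and the season-specific logistic regressions with food security as a predictor do not need the between-visit contrast.

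All of this stands, and it limits the certainty and the size. It does not remove the point. The month-frequency answers are in the scoring rule as published. They fit worst with the short windows that would preserve the contrast, and the same score is to be tested as a seasonal difference.

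**Conclusion.** The point holds, conditional on the recall window. The published scoring implies a look-back of several months, and nothing ties it to the current monsoon. For windows of about six months or more, the difference in season coverage between visits is close to nothing (0.12/0.01 at six months), slightly reversed (-0.14/-0.17 at nine) or nil (0/0 at twelve). In that range a change in score between visits cannot be attributed to the monsoon and may reflect year-on-year or pandemic change. At about three months the contrast is diluted to roughly one half to two thirds of full separation, with mislabelled forms near season onset.

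The figures rest on a 25 May season start, follow-up in 2022 and evenly spread visit days. As a guide to attenuation they also assume equal weighting of months. The result at twelve months does not depend on the visit dates.

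This is more than missing detail, because following the plan as written can produce a wrong seasonal conclusion.

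**What to change.** State the recall window actually used in the baseline questionnaire, then act on it.

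- **About six months or longer:** remove food security as an outcome from the seasonal paired test and the mixed model. Keep it for Objective 1 and as a household-level covariate or predictor. State that no seasonal change in food security can be concluded.
- **About three months:** keep the test, report the dilution with the actual visit dates, and flag visits near season onset.
- **In between:** repeat the count above with the actual window and visit dates before deciding.

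Baseline collection finished on 30 April 2022, so a short recall period at both visits is no longer possible for this cohort. A short-recall form may be added at follow-up for within-season association only. The existing cut-offs should not be assumed to carry over to it.

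The cost is a few sentences, and the data had not been processed for analysis when the article was submitted. The downside is that the seasonal food-security part of Objectives 2 and 3 is narrowed or dropped.
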